### Interim analysis plan

All safety events will be reviewed in real time by the PIs and the Data Safety Monitoring Committee (DSMC) chair on a case-by-case basis. They will be reported to the REB shortly after being identified. As our population is critically ill and the baseline incidence of death is high, each death will be adjudicated by the co-PIs and chair of the DSMC as related to the intervention or not.

The DSMC will review data on all possibly related AEs and SAEs after 175 patients (i.e., 50% of total planned recruitment). If the one-sided *p*-value is < 0.1 for cumulative SAE, then an interim two-sided analysis of the primary outcome will automatically be conducted. This analysis will generate a conditional power for showing efficacy in the final analysis of the primary outcome, assuming that the group-specific event rates observed to date remain the same in the total sample size. If the conditional power for efficacy is < 20%, in the context of a one-sided *p* < 0.1 for any of the safety outcomes, then the DSMC will recommend stopping the trial to the Steering Committee. The DSMC may make a similar recommendation even if these exact thresholds are not met, based on its interpretation of the balance between safety and efficacy.

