### Data Safety Monitoring Committee

As per the FDA guidance document the Establishment and Operation of Clinical Trial Data Monitoring Committees for Clinical Trial Sponsors, a DSMC will oversee the safety of the trial patients. The DSMC is comprised of three members who remain completely independent of the study investigators. The DSMC members all have extensive trial experience and include a senior methodologist who has served as Chair on numerous DSMCs for international RCTs, a senior biostatistician, and an intensivist. The DSMC will be responsible for safeguarding the interests of study patients, for assessing the safety and efficacy of study procedures, and for monitoring the overall conduct of the study. The DSMC will periodically review enrollment and demographic summaries, listings of protocol deviations, and summaries and listings of SAEs. In accordance with a pre-specified DSMC Charter, the DSMC will advise the Executive and Steering Committees on any concerns related to patient safety and trial conduct and will make recommendations for the study to continue as designed, for study termination, for study continuation with major or minor modifications, or temporary suspension of enrollment until some uncertainty is resolved.

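### Relatedness calls that the DSMC chair shares with the co-PIs can filter the safety data the DSMC then judges; the committee should receive all deaths and SAEs by arm, whatever their attribution

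*Protocol article*

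**What the plan says.** All references are to the protocol article.

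- **Interim analysis plan, first paragraph.** The chair has two tasks shared with the investigators. The first is continuous case review: "All safety events will be reviewed in real time by the PIs and the Data Safety Monitoring Committee (DSMC) chair on a case-by-case basis". The second is attribution of deaths: "each death will be adjudicated by the co-PIs and chair of the DSMC as related to the intervention or not".
- **Interim analysis plan, second paragraph.** The formal review is defined by attribution: "The DSMC will review data on all possibly related AEs and SAEs after 175 patients". A test follows: "If the one-sided *p*-value is < 0.1 for cumulative SAE, then an interim two-sided analysis of the primary outcome will automatically be conducted". Conditional power below 20%, together with a one-sided p < 0.1 on any safety outcome, leads to a recommendation to stop. The DSMC may also make that recommendation when the thresholds are not met.
- **Data Safety Monitoring Committee.** "The DSMC is comprised of three members who remain completely independent of the study investigators". The committee is responsible "for assessing the safety and efficacy of study procedures, and for monitoring the overall conduct of the study". It also receives SAE summaries and listings periodically, and a charter is mentioned but not shown.
- **Safety outcome measures.** Being judged related to study treatment is one route by which an event in this population counts as an AE or SAE. The other is the local principal investigator's judgement that it lies outside the expected course.

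**The concern.** A monitoring committee protects patients by looking at outcomes by arm without depending on the investigators' view of what caused them. Here the attribution of each death is a joint product of the co-PIs and one of the three DSMC members, and the formal interim review is described in terms of attributed events.

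In this population most deaths will have a plausible explanation in the underlying illness. If the drug raised mortality modestly, the individual deaths could each reasonably be called unrelated, and the excess would show only in a comparison of all deaths between arms. The stated review does not ask for that comparison.

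A second, smaller matter is that the article does not say whether the chair is blind to allocation when adjudicating, or whether the chair goes on discussing cases with the blinded co-PIs after a review by arm.

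**Working it through.** The plan gives no figure to reproduce on this point, so the check is mainly a comparison of sections.

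**Step 1: who classifies and who judges.** Interim analysis plan puts the chair among those who attribute each death. Data Safety Monitoring Committee puts the same person on the body that assesses safety. That is an overlap of one member in three.

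**Step 2: whether the classification reaches the DSMC's data.** The review at 175 patients (175/350 = 50%, as stated) covers possibly related events. A death classed as unrelated is outside that description. The trigger is worded as cumulative SAE, without saying whether unrelated deaths count. Read with the sentence before it and with Safety outcome measures, attribution can plausibly affect that count as well. This is a reading, not an explicit statement.

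**Step 3: whether a few calls could matter.** The article gives no SAE counts and names no test, so the counts below are assumptions. Inputs are 88 and 87 patients per arm at the interim (175 in total) and a pooled one-sided z test:

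z = (a/88 − b/87) / √[p(1 − p)(1/88 + 1/87)], with p = (a + b)/175.

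For a = 6 and b = 2: p = 8/175 = 0.0457, the difference is 0.0682 − 0.0230 = 0.0452, the standard error is 0.0316, z = 1.43 and one-sided p = 0.076.

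| Counted SAEs (a vs b) | One-sided p | Trigger at p < 0.1 | One fewer in the first arm | One-sided p | Trigger |
|---|---|---|---|---|---|
| 6 vs 2 | 0.076 | met | 5 vs 2 | 0.127 | not met |
| 9 vs 4 | 0.078 | met | 8 vs 4 | 0.120 | not met |
| 12 vs 6 | 0.071 | met | 11 vs 6 | 0.105 | not met |

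With Fisher's exact test the switch moves but remains: 7 vs 2 gives p = 0.087 (met) and 6 vs 2 gives p = 0.143 (not met). These pairs were chosen near the threshold. They show that with small counts one attribution can turn the trigger on or off. They do not show how often that would happen, or that the chair's involvement makes a call wrong.

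**Step 4: what the chair knows.** Blinding lists intensivists, research and ICU personnel, patients, the Executive and Steering Committees and the data analysts. Reducing bias adds outcome assessors and adjudicators. Neither names the DSMC. Between-arm p-values and conditional power require data separated by group, but no section says whether the chair sees them, or in what form.

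**The case against.** The strongest reply is that the text contains no contradiction. Independence under Data Safety Monitoring Committee can mean independence of membership: the three are not investigators, and joining a case review does not make the chair one. The arrangement can even be seen as a safeguard, since an outsider checks the co-PIs' attributions. This stands as far as it goes. The conflict is one of function, not of wording, and it would be too strong to say that the declared independence is false.

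Several mitigating points also stand. The joint adjudication concerns deaths only. The co-PIs are meant to be blinded, so misattribution should not systematically favour one arm. The periodic SAE listings are not limited to related events. All-cause mortality at 60 and 90 days is a secondary outcome that attribution cannot change. The DSMC may act outside its thresholds. None of these makes the formal review at 175 patients a comparison of all deaths by arm.

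A reader might infer more, namely that the chair has arm-level results and will unblind the co-PIs, or else must stay blinded and leave the committee a member short. The documents support neither. Deaths can be adjudicated without knowledge of the patient's allocation, and grouped or coded summaries do not reveal individual allocations. Access rules commonly sit in a charter, so their absence from an article is not a fault.

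A reader might also multiply an assumed mortality by 350 to size the problem. At 20% to 35% that gives 70 to about 122 deaths (350 × 0.20 = 70; 350 × 0.35 = 122.5). The mortality range is not in the article, and the product measures workload, not bias.

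**Conclusion.** The point holds in a limited form. A judgement-based classification, made jointly by the investigators and one of three DSMC members, can filter the safety data on which the committee's formal interim review rests. An imbalance in deaths classed as unrelated could remain outside that review as written. This is a weakness in a design choice and a poor fit between two sections, not an outright contradiction.

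No size of effect can be derived from the documents. The sensitivity of the p < 0.1 trigger rests on assumed counts and on reading cumulative SAE as affected by attribution. Information passing from the chair to the co-PIs is a possible route only. The point is minor, but it bears on patient safety and is cheap to correct.

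**What to change.** Amend Interim analysis plan so that at 175 patients the DSMC receives all deaths and all recorded SAEs by arm, regardless of attribution, with the relatedness classification alongside as secondary information. State whether the cumulative-SAE trigger counts events irrespective of attribution.

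Reconcile that section with Data Safety Monitoring Committee, and align the charter, by stating two things: any adjudication of deaths is done blind to allocation, and a DSMC member who has seen results by arm takes no further part in case adjudication with the blinded co-PIs.

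The chair need not be replaced by Steering Committee members. That committee receives any recommendation to stop, so having its members classify the deaths would raise a similar question.

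The cost is a change of wording and slightly longer DSMC reports. Table 2 already schedules collection of ICU or hospital death, so no new data collection is needed for deaths. The drawback is statistical: background deaths add noise to the safety comparison, which is a reason to keep the relatedness classification visible beside the full counts. Because Safety outcome measures uses relatedness in deciding what becomes an SAE, the all-deaths comparison is the part of the report that attribution cannot affect.

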#### Primary outcome measure

The primary outcome is:
The length of ICU stay as measured in hours. We will include both timing of discharge decision and actual departure from ICU.

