### Data analysis

#### Patient-centered analysis

All analyses will follow the intention-to-treat (ITT) principle. Analyses of the primary and secondary outcomes (i.e., patient-centered outcomes) will involve summary measures obtained by aggregating the endpoints using Stata software package (StataCorp, TX, USA). We will compare median differences along with their 95% confidence intervals. Baseline comparisons will be performed using the chi-squared test for equal proportions with results to be reported as numbers, percentages, and 95% confidence intervals. Continuous normally distributed variables will be compared using paired *t*-tests and reported as means with 95% confidence intervals, while non-normally distributed will be compared using Wilcoxon rank sum tests and reported as medians and interquartile ranges.

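### The interim stopping rule projects event rates for an outcome measured in hours and names two different safety triggers

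*Protocol article*

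**What the plan says.** The Interim analysis plan sets one formal review: "The DSMC will review data on all possibly related AEs and SAEs after 175 patients", which is half of planned recruitment. A two-step rule follows.

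- **Step 1, opening the look.** The condition is "If the one-sided *p*-value is < 0.1 for cumulative SAE". If it is met, a two-sided interim analysis of the primary outcome follows automatically.
- **Step 2, stopping.** That analysis gives a conditional power for final efficacy, calculated "assuming that the group-specific event rates observed to date remain the same in the total sample size". If it is below 20%, "in the context of a one-sided *p* < 0.1 for any of the safety outcomes", the DSMC recommends stopping. The DSMC may also recommend stopping when the thresholds are not met.

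Under Primary outcome measure, the outcome is "The length of ICU stay as measured in hours". Under Patient-centered analysis, the plan is: "We will compare median differences along with their 95% confidence intervals". No event is defined for this outcome.

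The Interim analysis plan also has every death adjudicated as related to the intervention or not. Under Safety outcome measures, laboratory changes, signs and symptoms need not count as AEs or SAEs unless they are considered treatment-related or, in the local investigator's judgement, do not fit the underlying illness and expected course.

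**The concern.** A numeric stopping rule should let two statisticians with the same interim data reach the same answer. This one does not, for two reasons.

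First, conditional power needs an assumption about the remaining data on the scale of the final test. The stated assumption concerns event rates, which hours of ICU stay do not have. The quantity compared with 20% is therefore not defined for this endpoint.

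Second, the two sentences name different safety conditions. Which one governs determines how often the trial's efficacy data are opened when there is no harm, and whether a signal in a single event type, such as bowel or limb ischemia, can lead to the automatic stop.

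A third and smaller worry is the relatedness wording. The section itself notes that baseline mortality is high. Case-by-case attribution is hard in such a population, and a comparison between arms is what would show an excess of deaths. The automatic trigger does not clearly contain that comparison.

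**Working it through.** **Plan's own figures.** 161/(1 − 0.08) = 175 per arm, so 350 in total, and 0.5 × 350 = 175. The interim timing reproduces, and I take the information fraction as t = 0.5.

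**Outcome against rule.** The outcome is in hours and its summary is a median difference. The conditional-power input is an event rate per group. Nothing in the article links the two.

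**Trigger logic, case by case.**

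- Cumulative SAE p < 0.1: the look opens and conditional power exists. If cumulative SAE counts as a safety outcome, the second safety condition is already met and adds nothing. If it does not count, a further signal is needed.
- Cumulative SAE p ≥ 0.1, one single outcome p < 0.1: no look, no conditional power, no automatic stop.
- Neither: nothing happens.

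So the reference to any safety outcome either does no work, or narrows the rule, or shows that a different trigger was meant.

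**Conditional power, restated on the test statistic under the current trend** (two-sided alpha 0.05):

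CP = Φ[(Z/√t − 1.96)/√(1 − t)]

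Setting CP = 0.20 at t = 0.5: Z/√0.5 = 1.96 − 0.842 × 0.707 = 1.365, so Z = 0.965.

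- No effect: P(Z < 0.965) = 0.833.
- Design effect (80% power): drift = 1.96 + 0.842 = 2.80, so the interim mean of Z is 2.80 × √0.5 = 1.98, and P(Z < 0.965) = Φ(0.965 − 1.98) = 0.155.

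**Automatic stop by the written route, no excess harm.** The cumulative-SAE test opens the look with probability 0.10. If safety and efficacy statistics are independent:

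- No effect: 0.10 × 0.833 = 0.083.
- Design effect: 0.10 × 0.155 = 0.0155.

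These are upper values, because the second safety condition can only lower them. Without independence, the ceiling is the 0.10 of the trigger itself.

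**If any safety outcome were the trigger.** The chance of at least one p < 0.1 with no true harm, for k independent outcomes, is 1 − 0.9^k:

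- k = 3: 1 − 0.729 = 0.271.
- k = 6: 1 − 0.531 = 0.469.

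The article does not say how many outcomes are meant. Table 2 lists six named event groups, so k = 3 to 6 is my assumed range. Correlated outcomes would give lower figures.

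**If all-cause mortality were added to cumulative SAE as a second trigger:** 1 − 0.9² = 0.19 if independent.

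**The case against.** The strongest reply is that the intent is recoverable. The sentence means that what has been seen in each arm continues, which is ordinary current-trend conditional power, and the working above computes it without difficulty. That is fair. A reader might infer that the calculation is impossible, and this goes too far: the wording is wrong for the endpoint, but the idea behind it is clear. The DSMC Charter, which is not shown, may also give a formula. The published sentence remains incorrect all the same.

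On the triggers, the two phrases can be read as compatible if cumulative SAE is itself one of the safety outcomes. The second phrase is then redundant, and the stop probability stays at the low values of the written route. A reader might instead combine the 27% to 47% with the chance of low conditional power and report a high false-stop rate. The text does not support that, because no conditional power exists until the cumulative-SAE condition has been met. Nor is stopping an ineffective treatment for low conditional power an error in itself; the error that matters is the one at the design effect.

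On deaths, a reader might infer that the DSMC could not see an excess. The documents say otherwise. The wording is possibly related, not related, and it may qualify AEs only. The cumulative-SAE condition does not repeat it. Under Safety outcome measures, events that do not fit the underlying illness also count. The DSMC chair takes part in adjudicating every death, the DSMC section provides SAE summaries and listings with no stated relatedness filter, and the DSMC may act outside the thresholds. Nothing in the article says how most deaths would be attributed. What stands is narrower: discretion does not make the written rule consistent, and the automatic trigger does not clearly include all-cause death by arm.

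**Conclusion.** The point holds in two main parts and one lesser part.

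1. The conditional-power assumption does not fit the primary outcome and has to be restated on the scale of the primary test.
2. The look and the stop clause use different safety conditions. As written, a single-outcome signal without a cumulative-SAE signal cannot reach the automatic stop. The stop probability by that route is small: at most about 8% with no effect and 1.5% at the design effect, given no excess harm, t = 0.5, current-trend conditional power, and independent safety and efficacy statistics. What is unsettled is the intended trigger, whose false-alarm chance is 10% under one phrase and about 27% to 47% under the other (three to six outcomes, number and independence assumed).
3. The relatedness wording leaves it unclear whether all-cause death by arm enters the automatic trigger. This is a gap in the trigger only, given the DSMC's wider access and discretion.

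The rule should be corrected before the 175-patient review, because the correction is nearly free and changes what the rule does.

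**What to change.** - **Conditional power.** Replace the event-rate assumption with the observed treatment effect on the same test statistic as the final primary analysis, carried forward as the current trend at an information fraction of about 0.5.
- **Trigger.** Reconcile the two sentences so that one and the same safety condition opens the look and supports the stop recommendation. If it covers several outcomes, list them and state the resulting false-alarm chance.
- **Deaths and named events.** State that the 175-patient review compares all-cause mortality and the Table 2 events by arm regardless of attribution.

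The cost is a change of wording in the protocol and the DSMC Charter. Deaths and the Table 2 events are already collected. Making mortality part of the automatic trigger is optional; it would raise the false-alarm chance from 10% to about 19% if the two tests are independent.

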### Registration

An initial ‘No Objection Letter’ was received from Health Canada on April 3, 2020 (HC6-24-c236428), and the trial was registered on www.clinicaltrials.gov on July 28, 2020 (NCT04489589). A systematic review and meta-analysis will be registered with PROSPERO (https://www.crd.york.ac.uk/prospero/).

### Data management

Clinical site research personnel will enter all patient data into the REDCap system. Briefly, the REDCap system will be managed and housed within the Department of Critical Care Medicine (DCCM) Research Office, located at the University of Alberta, Edmonton, Alberta, Canada. Personnel within DCCM Research Office will be responsible for programming and maintaining the database. With the support from the DCCM Research Office, personnel with the coordinating center will be responsible for daily data management.

### Monitoring

Multiple measures are in place for data quality control. These measures include (1) on-site training of research and clinical personnel; (2) standard operating procedures to guide storage, preparation, and administration of the study drug; (3) ongoing assessment of performance and periodic feedback to the clinical sites on performance with benchmarking from other sites; (4) site monitoring visits (remotely or in person); (5) ongoing review of missing data and outliers; and (6) rapid dissemination of responses to frequently asked questions via our study website and monthly newsletter. Coordinating center personnel and the principal investigators will be available to answer study-related questions.

### Auditing

A formal audit will be conducted by the coordinating center at regular intervals as per institutional policy. In addition, this study may be audited by other governing regulatory bodies including the University of Alberta and Health Canada.

### Data Safety Monitoring Committee

As per the FDA guidance document the Establishment and Operation of Clinical Trial Data Monitoring Committees for Clinical Trial Sponsors, a DSMC will oversee the safety of the trial patients. The DSMC is comprised of three members who remain completely independent of the study investigators. The DSMC members all have extensive trial experience and include a senior methodologist who has served as Chair on numerous DSMCs for international RCTs, a senior biostatistician, and an intensivist. The DSMC will be responsible for safeguarding the interests of study patients, for assessing the safety and efficacy of study procedures, and for monitoring the overall conduct of the study. The DSMC will periodically review enrollment and demographic summaries, listings of protocol deviations, and summaries and listings of SAEs. In accordance with a pre-specified DSMC Charter, the DSMC will advise the Executive and Steering Committees on any concerns related to patient safety and trial conduct and will make recommendations for the study to continue as designed, for study termination, for study continuation with major or minor modifications, or temporary suspension of enrollment until some uncertainty is resolved.

